## Secondary trial outcome analysis

Outcomes at 12- and 24-weeks follow-up will be summarised by randomised group and overall using mean (SD) and median (IQR) for continuous variables and count (percentage) for categorical variables. The number of SAEs will be presented overall and by randomised group.  All exploratory analyses will be considered hypothesis generating rather than providing firm conclusions and no p values will be reported.

Outcome acceptability will be determined by quantifying the amount of missing data across the secondary outcomes. The proportion of missing data (number, %) will be reported for each outcome, but no imputation will be performed to account for this missing data. Reasons for missing data will be gathered where possible.

Quantitative acceptability data including:

- rates of uptake and engagement with each component of the PERSONAL-AGILITY intervention
- adherence to the intervention (e.g., frequency, intensity, time and type of activity)

will be reported descriptively using number and percentage.

PROMS relating to intervention acceptability (the 9-item shared decision-making questionnaire) will be examined descriptively, by reporting at 12- and 24-weeks follow-up using mean (SD) and median (IQR).

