# Trial design

This is a 24-week feasibility randomised controlled trial, with a mixed-methods process evaluation. The trial schematic on page 19 provides an overview of the trial design and core trial visits and process evaluation.

Fifty Individuals aged ≥18 years living with MLTCs and frailty will be enrolled. Participants will be approached via diverse means (including through primary care, secondary care and public advertisement/self-referral), before undergoing eligibility and consent procedures by telephone and/or in-person as required and preferred. Carers will also be invited to take part in the trial as part of a dyad.

Participants will be allocated in a 2:1 ratio in favour of the intervention group, to one of two groups:

- The PERSONAL-AGILITY intervention
- Ongoing USUAL care

Allocation will use stratification based upon frailty status. All participants will undertake three assessments:

- Visit 1 – Week 0 – Baseline Assessments
- Visit 2 – Week 12 – Intermediate Follow-Up Assessments
- Visit 3 – Week 24 – Final Follow-Up Assessments

These visits may be combined where participants take part as a dyad or may be conducted separately if participants prefer.

An embedded mixed methods process evaluation, combining quantitative data (see section 2.3.1) gathered within the trial with observational and qualitative interview data, will provide additional insights into the feasibility and acceptability of both the intervention and the study design. Interviews will be conducted separately to ensure free expression of views and opinions.

The process evaluation will assess the:

- Trials acceptability, including recruitment, procedures and outcomes
- Intervention
  - Implementation: fidelity, dose and reach
  - Potential mechanisms of impact
- Contextual influences.

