### Data collection

In addition to the quantitative acceptability data outlined in section 7.1.3, quantitative process data will include assessment of intervention fidelity. Due to the feasibility nature of this study, the intervention (apart from the physical activity officer sessions which will be delivered by the physical activity officers and community providers) will be delivered by the research team. Given that the intervention:

- Is complex and targets multiple behaviours (sleep, physical activity and sedentary behaviour) which are selected by the participants in line with a shared decision-making approach
- Can include both carers and people with MLTCs in a ‘dyad’

an assessment of intervention fidelity for those sessions provided by the research team will still provide useful data that will inform the future implementation of the intervention within a definitive trial and to refine a training package for intervention providers within this definitive trial.

Informed consent to audio record PERSONAL-AGILITY sessions will be sought from all participants. Audio-recording all sessions is the current gold standard for intervention fidelity assessment^108^. The fidelity assessment will be completed using audio recorded sessions and a fidelity checklist and coding manual developed by the study team. and will be undertaken by trained observers. This checklist and manual will be developed *a priori* by two researchers to ensure it accurately reflects the PERSONAL-AGILITY intervention, but will include the following areas:

- Duration and focus of the intervention
- Intervention providers’ behaviours consistent with a shared decision-making approach
- Behaviour change techniques used as intended
- Key messages, or content of the intervention is delivered as intended
- Digital tools and other resources and materials used as intended
- Adaptations made to the intervention

Where possible, two people will undertake the fidelity assessments and inter-rater reliability assessed. Once agreement is established, intervention fidelity assessments may be carried out by one researcher.

All sessions will be audio-recorded with audio-recordings from initial and follow-up assessments, physical activity officer sessions (where applicable) and follow-up phone calls included. Around 10% of the programme delivered will be analysed, which is consistent with recommendations within the literature ^108^.

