There may be some risks associated with becoming more active and sitting less. These include a slightly elevated risk of falls for people who have had a previous fall. Overall, previous research tells us that the benefits of being more physically active far outweigh the risks of active, and that in the long run sitting more does not make people at risk of falls safer. We will ensure that participants are well enough to take part in the programme as part of the screening process, and we will also make sure that they receive a programme which takes into account any previous falls you may have had to ensure that it is right for your needs. Some physical activities can be associated with short-term muscle aches which are normal, but can be uncomfortable, particularly if participants are not used to being physically active.

There are minimal risks associated with the interventions we will use to support participants to improve their sleep, but for some people with severe insomnia they may not be effective and could lead to frustration, or possibly worsening sleep habits. We will track this closely throughout the intervention, and refer these participants back to their GP if we suspect that they may need more in-depth support, or that they might have an underlying condition which requires treatment.

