## Reporting procedures for all Adverse Events

AEs that are deemed directly related to study activities which are observed by the investigator or reported by the participant will be recorded in the participant’s medical records and an AE log from the time the participant is randomised. The following information will be recorded: description, date of onset and end date, severity, assessment of relatedness to study, and action taken. Additional follow-up information should be provided as necessary. AEs considered related to the study as judged by a medically qualified investigator or the sponsor will be followed until resolution, or the event is considered stable.  All related AEs that result in a participant’s withdrawal from the study or are present at the end of the study, should be followed up until a satisfactory resolution occurs.

It will be left to the investigator’s clinical judgement whether an AE is of sufficient severity to require the participant’s removal from treatment. A participant may also voluntarily withdraw from treatment due to what he or she perceives as an intolerable AE.  If either of these occurs, the participant must undergo an end of study assessment and be given appropriate care under medical supervision until symptoms cease or the condition becomes stable. The severity of events will be assessed using the following scale: 1 = mild, 2 = moderate, 3 = severe. AE’s will be recorded within the participant’s medical records and an AE log. Any safety concerns that arise because of this, will be reported to the sponsor as soon as possible.

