## Reporting Procedures for Serious Adverse Events

All SAEs (except from those outlined as expected) occurring from the time of randomisation until the final study visit must be reported to the Sponsor immediately and within 24-hours of becoming aware of the event. The SAE will be reported using appropriate forms and according to the Sponsor SOP for reporting serious adverse events. Additional information will be provided if requested to the Sponsor and main Research Ethics Committee (REC). The PI or a delegated physician (as agreed by the Sponsor) is responsible for the review and sign off of the SAE and the assessment of causality (i.e., whether an event is related to a study procedure or intervention).

The Sponsor will perform an initial check of the information and ensure that the SAE line listing is reviewed by the Director of Research & Innovation. All SAE information must be recorded on an SAE form and sent to the Sponsor. Additional information received for a case (follow-up or corrections to the original case) needs to be detailed on a new SAE form and sent to the Sponsor. Copies of all documentation and correspondence relating to SAEs will be stored in the trial master file (TMF).

For each **SAE** the following information will be collected:

- Full details in medical terms and case description
- Event duration (start and end dates, if applicable)
- Action taken
- Outcome
- Seriousness criteria
- Relationship to the study procedure or intervention

Any change of condition or other follow-up information should be emailed to the Sponsor immediately and within 24-hours of the information becoming available. Events will be followed up until the event has resolved or a final outcome has been reached.

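### Serious adverse events are to be shown as bare numbers by arm under 2:1 allocation, with more between-visit contact in one arm, so the intervention may look less safe than it is

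*Protocol*

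**What the plan says.** **Summary measure.** Section 9.5 says of harms: "The number of SAEs will be presented overall and by randomised group". The sentence before it prescribes count and percentage for categorical outcomes, but SAEs are given only as a number.

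**Arms.** Section 3 states "Fifty Individuals aged ≥18 years living with MLTCs and frailty will be enrolled" and "Participants will be allocated in a 2:1 ratio in favour of the intervention group". Up to 50 carers may join, and section 6.6.1 randomises each with the person they care for.

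**How an SAE enters the record.** Under section 8.4, SAEs from randomisation to the final study visit "must be reported to the Sponsor immediately and within 24-hours of becoming aware of the event". The trigger is awareness. Section 8.2 logs AEs "which are observed by the investigator or reported by the participant", but that rule covers AEs judged directly related to study activities and does not govern SAEs.

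**Contact common to both arms.** Section 3 says "All participants will undertake three assessments" (weeks 0, 12 and 24), and Table 1 schedules adverse event reporting for all participants at each.

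**Contact in the intervention arm only.** Sections 6.9 and 7.3.2 have the research team deliver most of the intervention. The fidelity work records these sessions, with "audio-recordings from initial and follow-up assessments, physical activity officer sessions (where applicable) and follow-up phone calls included". Section 7.1.2 adds an adherence diary that asks for reasons for non-adherence. Section 7.9.2 says of sleep problems "We will track this closely throughout the intervention". Section 6.10 leaves controls with their usual NHS providers and describes no trial contact between visits. Section 6.7 states that neither participants, providers nor outcome assessors are blinded.

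**The concern.** There are two separate problems, and both are likely to push the comparison the same way.

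The first is the measure. A bare count in arms of unequal size is expected to be higher in the larger arm even when risk is identical. Counts of events also let one person with several admissions dominate: Table 4 makes inpatient hospitalisation an SAE, and section 8.3 does not name it among the exempt expected events. Pooling carers with people living with frailty mixes two populations likely to differ in background risk and leaves the denominator anywhere from 50 to 100.

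The second is ascertainment. If awareness triggers reporting, extra routes to awareness in one arm can add events in that arm. An admission in week 5 may be mentioned at an intervention review or phone call, or in the diary. In the control arm the same admission waits for the week-12 visit and rests on recall, or on other sources if the visit is missed.

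This is the only between-arm harm summary that the protocol specifies, and section 9.4 says that the decision on a definitive trial will draw on all available data. An excess in the intervention arm would be hard to separate from arm size and closer observation.

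**Working it through.** The protocol gives no SAE rate and no safety calculation, so there is no figure of its own to reproduce.

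**Inputs from the protocol.** N = 50 people with MLTCs and frailty and 2:1 allocation (section 3). 50 × 2/3 = 33.3 and 50 × 1/3 = 16.7, taken as 33 and 17.

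**Assumptions, not in the protocol.** 0.1 to 0.4 SAEs per person over 24 weeks, the same in both arms; event counts independent and Poisson; control-arm capture of 50% to 100% relative to the intervention arm. Carers are left out.

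**Step 1: allocation alone, equal risk and equal capture.** Expected count = rate × n, so the expected count ratio is 33/17 = 1.94 at every rate.

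| SAEs per person | Expected, intervention v control | P(intervention count higher) | P(intervention rate per person higher) |
|---|---|---|---|
| 0.1 | 3.3 v 1.7 | 0.69 | 0.57 |
| 0.2 | 6.6 v 3.4 | 0.81 | 0.54 |
| 0.3 | 9.9 v 5.1 | 0.87 | 0.53 |
| 0.4 | 13.2 v 6.8 | 0.91 | 0.52 |

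Dividing by the number randomised removes this effect. At a rate of 0.2, 6.6/33 = 3.4/17 = 0.2, a rate ratio of 1.00.

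**Step 2: unequal capture, true rate 0.2 in both arms.** If a fraction c of control SAEs is captured for full capture in the intervention arm, the apparent rate ratio is 1/c and the count ratio is 1.94/c.

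| c | Apparent rate ratio | Count ratio | P(intervention rate per person higher) |
|---|---|---|---|
| 1.0 | 1.00 | 1.94 | 0.54 |
| 0.9 | 1.11 | 2.16 | 0.60 |
| 0.8 | 1.25 | 2.43 | 0.67 |
| 0.7 | 1.43 | 2.77 | 0.73 |
| 0.5 | 2.00 | 3.88 | 0.85 |

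Denominators do not repair this part. The table shows how sensitive the comparison is to c; it does not estimate c. Much of each count ratio is the allocation ratio of 1.94 and should not be read as ascertainment bias.

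**The case against.** **Denominators may be in the analysis plan.** Section 9.5 does not exclude n/N or percentages, table layout is often settled later, and the CONSORT diagram (section 9.2) will show group sizes. This has weight: the allocation effect can be cured at reporting. But the protocol does name the summary, and it is a poor one. Participants affected cannot be recovered from a published event count.

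**Control SAEs are not simply lost.** A reader might infer that the team sees only the intervention arm and that control events between visits go unrecorded. The documents do not support that. Table 1 schedules reporting for everyone at weeks 12 and 24, and deaths and admissions are plausibly picked up there. Section 7.8 plans GP contact and a review of health care databases for people who cannot be reached. Every participant's GP is told of the allocation (section 6.6.1). What remains is that these checks are meant to establish health status and are not described as SAE collection.

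**The direction is not certain.** Section 7.9.3 accepts that burden may be greatest in the intervention group. Higher dropout there would lower its capture. Some of the extra contact is also limited: officer sessions apply only to some participants and are not run by the research team, and the close tracking in section 7.9.2 concerns sleep.

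**Consequences are limited.** No criterion in Table 5 uses SAEs, no p values are planned, and each SAE receives a causality assessment (section 8.4). These points stand and lower the stakes. Causality assessment by an unblinded team does not correct a difference in which events are found.

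**Conclusion.** The point holds in a limited form. As worded, section 9.5 yields a comparison in which equal risk gives an expected 1.94 times as many events in the intervention arm, with repeat events and carers pooled. That figure needs only the 33:17 split and equal risk per person. The arms also differ in described between-visit contact, so capture may be fuller in the intervention arm. How much fuller cannot be derived from the protocol: apparent rate ratios of 1.11 to 1.43 correspond to assumed control capture of 90% to 70% and are illustrations only.

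A reader might go further and conclude that the intervention will look less safe. The documents support only that it may. The allocation effect vanishes once counts are read against group sizes, and scheduled enquiry is the same in both arms. Showing SAEs by group is right in itself; the faults are the measure and the lack of a stated common method of enquiry. The measure can be mended at analysis, but the enquiry has to be settled before data are collected.

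**What to change.** 1. **Section 9.5.** Report participants with at least one SAE over the number randomised (n/N, %) with a 95% confidence interval, plus events per unit of person-time, by arm. Show people with MLTCs and frailty and carers separately.
2. **Section 8.4 and the case report form.** Use the same scripted SAE question in both arms at weeks 12 and 24, covering the whole period since the last visit. For those who miss a visit, supplement it from the medical record, to which section 6.5 already seeks consent, within whatever consent the participant has left in place.
3. **Source of each SAE.** Record how it first came to light (scheduled question, record, intervention contact, diary, interview or other). Keep all SAEs in the main by-arm table, so that no known event leaves the headline comparison, and add a sensitivity display limited to events found by the common route.

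Immediate reporting to the sponsor of any SAE, however learnt of, is unchanged.

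**Cost.** One form field, a scripted question at existing visits, and modest staff time for record checks in a trial of 50 people and their carers.

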## Analysis of the mixed methods process evaluation

### Quantitative analysis

Data from the structured observation tool will be analysed using descriptive statistics. Number (percentage) will be used for categorical variables and mean (standard deviation) for normally distributed continuous variables Skewed data will be reported using medians and interquartile ranges.

Other quantitative data from processes and PROMS relating to intervention implementation (the 24-hour Physical Behaviour Burden Questionnaire) will be examined descriptively, by reporting at 12- and 24-weeks follow-up using mean (SD) and median (IQR).

### Qualitative analysis

Qualitative data will be collected and analysed concurrently, to allow iterative refinement of the intervention to occur ^89^, ^115^. Reflexive thematic analysis will be used to guide qualitative data analysis ^130^. Researchers will independently familiarise themselves with the interview data by listening to the audio-recordings and reading and re-reading the transcribed data.

Reflexive thematic analysis involves six sequential but iterative stages where the research can move back and forth recursively as new insight is gathered and links between data made:

- Familiarisation: the research team will read and re-read the data to become familiar with the data, making notes and analytic observations and insights.
- Coding: Succinct labels (codes) that capture and evoke important features of the data that might be relevant to addressing the research question will be devised. These will be agreed with the research team through discussion before being applied across the dataset. Multiple rounds of coding may be undertaken and codes revised through this process.
- Generation of initial themes: Codes will be examined and collated into broader patterns of meaning (potential themes). Data relating to each candidate theme will be collated.
- Developing and reviewing themes: Candidate themes will be checked against the coded data and the entire dataset, to determine fit with the data and ability to answer the research questions. Themes will be further developed, combined, or discarded during this phase.
- Refining, defining and naming themes: TA detailed analysis of each theme will be developed, establishing the scope and focus of each. Names will be given to each theme.
- Writing up: Data will be combined together with analytic narrative before being contextualised in relation to existing literature.

The intervention programme theory, and NPT (as previously described) will provide a sensitising framework to guide analysis ^107, 106,^ alongside the recently published coding manual ^107, 106^.

## Mixed methods analysis

Following separate qualitative and quantitative data analyses for both the trial and process evaluation, all results will be integrated and compared against the progression criteria (section 9.4) to facilitate a comprehensive understanding of: ^131, 132, 115, 133^

- the acceptability of the PERSONAL-AGILITY intervention
- refinement of the initial intervention programme theory
- the feasibility of a definitive trial of this intervention
- optimisation of the definitive trial design.

Integrated analyses will be facilitated by a ‘joint display’, which combines the findings in a tabulated form. This display may be organised according to the primary feasibility outcomes and will be used to assess the ways in which the data sets agree (confirmed), complement (offered an expanded explanation) or contradict each other and outline how the qualitative results expand and contextualise the key results from the quantitative results ^133, 134^.

Following this, decision-making relating to progression to a definitive trial, will be facilitated by the ADePT (*A process for Decision-making after Pilot and Feasibility Trials)* tool, which was developed to make decision-making regarding feasibility explicit^135^. Briefly, this process includes:

- Systematically identifying potential concerns surrounding the feasibility of a definitive trial and assigning them to a specific typology (Type A: a problem only for the trial, Type B: a problem for the trial and in the real-world, Type C: a problem only for the real-world)
- Identifying the range of potential solutions alongside supporting evidence
- Assessment of the best solution available.

# Data management

## Data Flow Diagram

The below data diagram outlines the flow of data in the trial and the process evaluation. In summary, data collected at the NHS research site will be uploaded onto a secure trial database (RED Cap). Following database lock, feasibility, acceptability and qualitative and quantitative process evaluation will be conducted.

[figure not shown]

## Data collection and management

All hard and electronic copies of data collected in this study will be identified by a unique study identification code. The link between the participant and their study ID number will be retained by the host NHS organisation in a locked filing cabinet in a secure office environment and with access restricted to members of the research team. All electronic data will be password protected and accessible only by delegated members of the research team during the active phase of the study and until the data have been analysed. Paper copies such as CRFs will be stored in a locked cabinet.

All research data, whether online or paper-based, will be transcribed onto the research database (REDCAP) by a delegated member of the research team. All study documentation containing identifiable participant data will be pseudonymised and managed in accordance with ICH-GCP, UK Policy Framework for Health and Social Care Research and the most up-to-date version of the Data Protection Act 2018 and General Data Protection Regulation (GDPR). Anonymised and non-identifiable body composition, inclinometer and accelerometer data will be downloaded, and analysis facilitated, using bespoke software available via the University of Leicester, and therefore these anonymised non identifiable files will be stored on a secure University of Leicester R drive.

Where applicable, to facilitate Physical Activity Officers to identify appropriate and suitable community groups for participants, connect them with these groups, monitor their engagement with these groups and support them where needed, participant names, contact information (email, telephone number, address) and relevant health data (relevant past medical history, physical activity, sleep and score from objective function and patient reported outcome measures) will be shared between UHL and the relevant local authorities who employ the physical activity officers. This will facilitate the delivery of this component of the PERSONAL-AGILITY intervention. Data will be subject to GDPR and will be transferred between the controller and processor by secure email to a verified local authority email.

Personal identifiable information will not be included in any research database. Participant identifiable information will be destroyed 12 months after completion of the study unless participants have consented to be contacted about future research. If a participant wishes to withdraw, they will be documented as a withdrawal and their personal identifiable data will be destroyed, unless they have consented to be contacted about future research.

For the observations and qualitative interviews within the process evaluation, willingness to continue will be confirmed verbally prior to the start of the observation/interview. Audio recordings of interviews will be labelled with a study identifier and will be destroyed once transcription is complete. Data will be transferred to the transcription service using secure file transfer. Transcripts will be anonymised and securely stored six years post-study duration. Audio recordings of observations will be labelled with a study identifier and destroyed after the observational tool has been completed. Completed observational tools will include no identifiable data and will be securely stored for six years post-study duration. Qualitative data analyses will be facilitated by NVivo and therefore anonymised transcripts will be securely stored on University of Leicester R Drives.

Study data will be archived in line with UHL policy; currently six years post-study duration. Data management will be delegated to trained members of the research team and overseen by the CI. Quality control checks of the source data and data entered into the trial database will also be undertaken by the research team.

Participants who do not already use wearable technology to track their activity, sleep and sedentary behaviour will be provided with a FitBit for the duration of the intervention. In order to link Steps4health and MyHealthMapp to the FitBit, they will be required, and supported to, set up an account with FitBit. This will require them to supply their name, email address, password, date of birth, gender, height, weight. They will then be asked to sign into their account and select what elements of their data they would like to link to Steps4Health and MyHealthMapp from their FitBit.

FitBit is able to determine precise geolocation data for select features, including location from GPS signals, device sensors, Wi-Fi access points, cell tower IDs and IP addresses. This type of data is collected if the participant grant access to their location. This information is not required to participate in the intervention and participants will be informed that they can remove access using your Fitbit device or mobile device settings. Fitbit retains the data, collected by the device until the participant chooses to delete it or discontinue using Fitbit services. The participant has the right to access, manage, and delete the data collected by the FitBit. Through their account settings, they can remove specific data types or delete their account entirely, which will initiate the process of erasing their data from Fitbit's systems. Participants will be informed of this during the consent process and also at the end of the intervention, so that they may delete their FitBit account if they wish. This will not influence the data collected via MyHealthMapp and Steps4Health, which will be retained for the purposes of the study.

